## Data analysis

All analyses will be conducted with both intention-to-treat (ITT) and per-protocol (PP) methods. Participants who discontinue the treatment arm they were randomized to (includes switches to the other arm) will be considered as failures of the primary outcome.

### Primary outcome

The primary outcome will be assessed in a binary fashion: participants need to fulfill both criteria (successful induction and low levels of withdrawal) in order to be successful with the primary outcome. Outlier COWS scores will be checked and confirmed with the clinical records on an ongoing basis by the study coordinator. Effort will be made by the study team to avoid missing COWS scores during the study. In case of missing scores, multiple imputation will be used to impute the missing variables, and sensitivity analysis will be performed by once assigning failure to all the missing COWS score and then success to them, then describing and explaining the impact on the results. Fisher’s exact test will be used to compare two groups with a significance level set at 0.05. To demonstrate the effect size, we will use both unadjusted and adjusted odds ratios with 95% confidence intervals using logistic regression. In the latter, effect size will be adjusted for age, gender, and baseline COWS score in addition to allocated arm. Adjustment for baseline covariates will improve the sensitivity of the comparison.

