**Fig. 1 Fig1:**
[figure not shown]
Study schema

Eligible participants will be randomized on an allocation ratio of 1:1 to either of the two arms, using a blocked permuted block design with block sizes of 4 and 6. Randomization will be managed with the REDCap platform [23, 24]. Once randomized, participants will complete baseline assessments and be followed for 7 days. Towards the end of the intervention period, the physician in charge will inform all participants about follow-up treatments that are available to them. Participants will receive follow-up with their community addictions physicians and/or the CPAS outpatient clinic.

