## Sample size and power calculation

The sample size calculation for the binary primary outcome is based on testing for superiority in a parallel group clinical trial. As only case reports have been published on rapid micro-induction, we expect a success rate of 95% in the experimental arm based on the opinion of two addiction psychiatry experts familiar with the method. We expect a success rate of 10% in the control arm, as most participants in the arm are anticipated to experience moderate to higher levels of withdrawal, which is defined as having a COWS score of ≥ 13. A difference of such a magnitude, 85%, is deemed clinically meaningful. Using G*Power 3.1 software, the minimum required sample size to power a Fisher’s exact test to detect this difference between the two arms with a type I error of 0.05 and a type II error of 0.1 will be 12 (6 in each arm). Adjusting for an attrition rate of 10% (participants with incomplete COWS data, participants who have discontinued the treatment they were randomized, and participants who have discontinued both treatment and data collection procedures), the required sample size is 14. We aim for a sample size of 50 (25 each arm), as a larger sample size is not feasible due to cost and constraints.

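### The primary effect size is planned only as logistic-regression odds ratios, which at the planned success rates have no finite estimate in about one trial in three

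*Protocol article*

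**What the plan says.** The article's Data analysis section, under Primary outcome, compares a binary success indicator between arms by Fisher's exact test at the 0.05 level. For the size of the effect it states: "we will use both unadjusted and adjusted odds ratios with 95% confidence intervals using logistic regression". The adjusted model contains arm, age, gender and baseline COWS. No risk difference is planned, and nothing is said about a zero cell or separation. All analyses are to be run on both an intention-to-treat and a per-protocol basis.

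The Sample size and power calculation section gives the planning values: "we expect a success rate of 95% in the experimental arm", "We expect a success rate of 10% in the control arm" and "We aim for a sample size of 50 (25 each arm"). It expresses the clinically meaningful effect as the difference between the two proportions, 85%.

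Missing COWS scores are to be multiply imputed. In addition, "sensitivity analysis will be performed by once assigning failure to all the missing COWS score and then success to them".

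**The concern.** The planning rates lie near 0 and 1, and the arms are small. An arm with 25/25 or 0/25 successes is then a routine result. Maximum-likelihood logistic regression gives no finite odds ratio in that case, and a Wald interval around it carries no information. Adding covariates to a model with few failures in one arm and few successes in the other makes separation more frequent.

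Baseline COWS can make this worse. Success requires scores of 12 or less from baseline onward, so a baseline score of 13 or more is failure by definition.

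If the trial goes as planned, the effect measure named in the protocol may therefore not be estimable by the ordinary method. A substitute would then be chosen after the data are seen, in an open-label trial.

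A smaller issue sits in the same paragraph. The two missing-score scenarios give both arms the same value, so they do not show the range that the treatment effect could take.

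**Working it through.** **Inputs.** Success 95% versus 10%, 25 per arm, 10% attrition (Sample size and power calculation); 1:1 allocation (Overview of study design); discontinuations counted as failures (Treatment discontinuation and study discontinuation; Data analysis).

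**The plan's own figure.** The article gives a minimum size "with a type I error of 0.05 and a type II error of 0.1 will be 12 (6 in each arm"). Exact enumeration of Fisher's test at 6 per arm gives power 0.945 one-sided and 0.774 two-sided; two-sided, 7 per arm gives 0.919. The figure of 12 is thus reproduced with a one-sided test (the article does not state sidedness), and 12/(1 − 0.10) = 13.3, rounded up to 14, as stated. At 25 per arm two-sided power exceeds 0.999, so sidedness has no consequence here.

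**Unadjusted odds ratio.** The estimate is not finite if an arm has all successes or none. The reverse events (0/25 experimental, 25/25 control) are negligible, so

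P = 1 − (1 − p₁²⁵)(1 − (1 − p₂)²⁵).

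At the planned rates 0.95²⁵ = 0.277 and 0.90²⁵ = 0.072, so P = 1 − 0.723 × 0.928 = 0.329.

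| Rates, n per arm | All succeed, experimental | None succeed, control | Not finite |
|---|---|---|---|
| 95% v 10%, 25 | 0.277 | 0.072 | 0.329 |
| 90% v 10%, 25 | 0.072 | 0.072 | 0.138 |
| 85.5% v 9%, 25 | 0.020 | 0.095 | 0.113 |
| 95% v 10%, 22 | 0.324 | 0.098 | 0.390 |

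The third row multiplies both planned rates by 0.90, that is, it counts all 10% attrition as failure on top of them. The fourth approximates a per-protocol set with about 10% removed.

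**Adjusted odds ratio.** The documents give no covariate distributions, so these are assumptions: age and baseline COWS standard normal, 30 to 40% of participants in one gender, and COWS with a log odds ratio per SD of 0 to 2. Trials were simulated (3,000 to 4,000 per setting) and separation was detected by linear programming.

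- COWS effect 0 to 1 per SD: about 42 to 44% (43 to 45% with an even gender split).
- COWS effect 1.5: 44 to 48%.
- COWS effect 2: about 52 to 53%.
- 85.5% v 9%, covariates unrelated to outcome: 17%.
- 22 per arm at the planned rates, covariates unrelated: 49%.

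**What is obtained when the odds ratio is finite.** For 24/25 v 2/25, OR = (24 × 23)/(1 × 2) = 276. The standard error of its log is √(1/24 + 1/1 + 1/2 + 1/23) = 1.259, so the Wald 95% interval is 23 to 3255. The risk difference is 0.96 − 0.08 = 0.88, Newcombe interval 0.65 to 0.95. For 25/25 v 2/25 the odds ratio is infinite, while the risk difference is 0.92 (0.70 to 0.98).

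**Missing-score scenarios (illustrative counts, 4 unresolved per arm, two-sided Fisher).**

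- Known successes 15 v 5: all failure, 15 v 5, p = 0.009; all success, 19 v 9, p = 0.010; experimental failure and control success, 15 v 9, p = 0.16.
- Known successes 20 v 2, nearer the plan: opposite direction, 20 v 6, p = 0.0002.

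**The case against.** Four objections deserve weight.

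1. **Handling of a zero cell belongs in the analysis plan, which is not shown, and naming logistic regression does not exclude a penalised or exact version.** This is fair as to the missing detail, and absence of a separation rule alone would not be a finding. What stands is the stated choice: the only effect measure is an odds ratio, while the design is justified on a difference in proportions at rates where the odds ratio behaves worst.

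2. **The one-in-three figure needs rates of exactly 95% and 10%, and the 95% is expert opinion.** This stands. At somewhat less extreme rates the probability is 11 to 14% unadjusted. The per-protocol analysis moves it the other way.

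3. **A reader might infer that the trial could end with no usable result.** The documents do not support that. The primary inference is Fisher's exact test, which separation does not touch; for 25/25 v 2/25 its p-value is about 6 × 10⁻¹². The arm proportions would still be available, and anyone could derive a risk difference from them.

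4. **A reader might also infer two faults in the missing-data plan.** One is that Fisher p-values will be pooled over imputations by Rubin's rules. The article never says how imputations are combined, so that is not a fault in the text. The other is that the same-direction scenarios hide a fragile conclusion. Near the planned rates they do not, as the 20 v 6 result shows; the example that loses significance lies far from the plan. Missingness is also limited, because discontinuations already count as failures and any recorded score of 13 or more settles the outcome.

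**Conclusion.** The point holds for the effect estimate and its interval, and for nothing beyond them. At the planned rates and size the ordinary maximum-likelihood odds ratio has no finite value in 33% of trials: 28% from 25/25 in the experimental arm and 7% from 0/25 in control, with a small overlap. That calculation is exact, given the rates.

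The adjusted figure of about 42 to 44%, rising to about 53% with a strongly prognostic baseline COWS, rests on covariate assumptions that the article does not supply. Both fall if the true rates are less extreme, to 14% unadjusted at 90% v 10%, and to 11% unadjusted and 17% adjusted at 85.5% v 9%. The superiority test is sound on this point.

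The missing-score scenarios are a secondary weakness. They do not bracket the treatment effect, but this is likely to matter only if the observed effect is much smaller than planned.

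The change should be made because a better-fitting measure is available at almost no cost and can be fixed before any outcome is seen.

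**What to change.** - Report the risk difference with a Newcombe or Miettinen-Nurminen 95% confidence interval as the main effect measure beside Fisher's exact test.
- Keep the unadjusted and adjusted odds ratios, but estimate them by Firth penalised logistic regression with profile-likelihood intervals, stated in advance.
- Add one missing-score scenario: missing counted as failure in the experimental arm and as success in the control arm.

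The cost is wording and slightly more analysis work, with no new data. The article reports that the site was still preparing for recruitment in November 2020. Firth estimation pulls the odds ratio toward 1. In the unadjusted model it is equivalent to adding 0.5 to each cell, so 24/25 v 2/25 gives (24.5 × 23.5)/(1.5 × 2.5) = 154 in place of 276. The odds ratio implied by the planned rates is (0.95 × 0.90)/(0.05 × 0.10) = 171. The report should state that the estimate is penalised.

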### Secondary outcomes

Secondary outcomes will be compared between two arms using Fisher’s exact, Wilcoxon–Mann Whitney, and interaction terms from Linear Mixed Models for binary, interval, and repeated measures, respectively.

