## Study design

### Overview of study design

This study is a randomized controlled trial comparing the effectiveness and safety of rapid micro-induction versus standard induction of buprenorphine/naloxone. It has received approval from the Research Ethics Board of the University of British Columbia (H19-03254) and is registered in clinicaltrials.gov (NCT04234191). In this open-label superiority trial, eligible patients with OUD will be randomized to either: (a) the rapid micro-induction arm or (b) the standard induction arm (treatment as usual).

The study schema is presented in Fig. 1. The study will take place at one site, Vancouver General Hospital (VGH) in Vancouver, British Columbia, Canada. The Complex Pain and Addiction Services (CPAS) is a consulting service in which VGH inpatients with substance use disorders are referred to for treatment and counselling. The study staff at CPAS will pre-screen referrals to determine general eligibility for participation in the study. Patients will then be invited by the study staff to complete the informed consent procedures. Once informed consent is provided, participants will undergo screening procedures to confirm their eligibility.

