### Secondary outcomes

The secondary outcomes are treatment retention, illicit drug use, self-reported drug use behaviour, craving, pain, physical health, safety, and client satisfaction.

Treatment retention will be assessed by buprenorphine/naloxone prescription pick-up on day 7.

Illicit drug use will be assessed by urine drug screens, which will analyze for the presence of cocaine, opioids including methadone, buprenorphine, hydromorphone, oxycodone, morphine, heroin, and fentanyl, benzodiazepines, amphetamines, and methamphetamine. Urine will be collected at screening, baseline, and after induction has been completed (day 3 of the experimental arm, and day 2 of the control arm).

Self-reported drug use behaviour will be assessed by the Treatment Outcome Profile (TOP) at baseline, and after induction has been completed (day 3 of the experimental arm, and day 2 of the control arm). The TOP is a 20-item instrument designed to assess and monitor substance misuse by measuring four different domains (substance use, health, crime and social functioning) and includes thirty-eight frequency, rating scale and period prevalence measure [30].

Craving and pain will be measured by numeric rating scales (NRS) at baseline, days 1 to 2 of the experimental arm, and day 1 of the control arm. The NRS for craving and pain will be administered every time the COWS is administered. The NRS presents the participant a rating scale which represents the spectrum of pain or craving: the left end indicates no pain or craving while the right end indicates extreme pain or craving [31]. Participants rate their pain or craving from 0 to 10.

Physical health will be assessed by the health section of the Opiate Treatment Index (OTI) at baseline. The OTI is a structured interview designed to provide a measure of the effectiveness of drug treatments, by measuring six outcomes: drug use, HIV risk-taking behaviour, social functioning, criminality, health status, and psychological functioning [32]. Only the health section of the OTI will be used; the health section is composed of items addressing signs and symptoms in major organ systems and injection-related health problems.

Safety will be assessed by the appearance of adverse events (AEs) and serious adverse events (SAEs), which will be recorded on the CRF. AEs and SAEs are defined in “Safety” section.

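### Post-induction TOP scores are to be compared without a stated baseline adjustment; the named tests are valid, but usually less precise than a baseline-adjusted comparison

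*Protocol article*

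**What the plan says.** The protocol article's outcomes section schedules the TOP twice: "Self-reported drug use behaviour will be assessed by the Treatment Outcome Profile (TOP) at baseline, and after induction has been completed". The second assessment falls "after induction has been completed (day 3 of the experimental arm, and day 2 of the control arm"), and Table 3 agrees. The instrument contains "thirty-eight frequency, rating scale and period prevalence measure", so its items are of mixed type.

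Under Data analysis, Secondary outcomes, a single sentence covers all secondary outcomes. It lists Fisher's exact test, "Wilcoxon–Mann Whitney, and interaction terms from Linear Mixed Models", matched in that order to binary, interval and repeated-measures outcomes. It does not say which of these the TOP receives, and it mentions no covariate.

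For the primary outcome, the same section reports the odds ratio both unadjusted and adjusted for age, gender and baseline COWS, and states that such adjustment makes the comparison more sensitive.

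Two design facts also bear on the point. The overview describes the study with the words "In this open-label superiority trial", and on the order of events it says "Once randomized, participants will complete baseline assessments and be followed for 7 days".

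**The concern.** A non-binary TOP score can reach the stated methods by two routes. Treated as an interval outcome, it goes to a Wilcoxon test of the post-induction values, and the baseline value is not used. Treated as a repeated measure, it goes to the arm-by-time interaction. With two visits and a separate baseline mean for each arm, that interaction is the difference between arms in mean change.

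Neither route handles chance baseline imbalance well. The first leaves it in. The second subtracts all of it, although only a fraction carries forward when the correlation is below 1. With 25 per arm, the standard error of a baseline difference is √(2/25) = 0.28 SD, so imbalances of that order are to be expected.

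At stake is the precision of one secondary outcome in a trial whose authors say that they cannot enlarge it. Type I error is not at issue.

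**Working it through.** **Inputs.** From the article: 25 per arm, 1:1 allocation, one baseline and one post-induction TOP. The article gives no SD, correlation or power for the TOP, and its sample-size calculation concerns only the primary outcome, so there is no stated figure to reproduce. Assumed: correlation ρ between baseline and follow-up of 0.3 to 0.7 (with 0 as a limit), equal SDs at both visits, two-sided 5% level, and an effect of 0.8 SD for the power comparison.

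**Variance of the arm contrast, relative to comparing post-induction means only.**

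- Post-only: 1
- Interaction with free baseline means (change score): 2(1 − ρ)
- Baseline-adjusted (ANCOVA): 1 − ρ²
- Adjusted over interaction: (1 − ρ²)/[2(1 − ρ)] = (1 + ρ)/2

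| ρ | Post-only | Interaction | Adjusted | Adjusted / interaction |
|---|---|---|---|---|
| 0.3 | 1 | 1.40 | 0.91 | 0.65 |
| 0.5 | 1 | 1.00 | 0.75 | 0.75 |
| 0.7 | 1 | 0.60 | 0.51 | 0.85 |

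Estimating the baseline slope costs a factor of about 1 + 1/(2n − 4) = 1 + 1/46 = 1.02 at n = 25. At ρ = 0 the adjusted analysis is therefore about 2% worse than post-only.

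**Detectable difference at 80% power**, (1.96 + 0.84) × √(2v/25), where v is the relative variance. At ρ = 0.5 it is 0.79 SD for post-only, 0.79 SD for the interaction and 0.69 SD for the adjusted comparison (large-sample factors).

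**Does the gain survive for rank methods?** The factors above apply to linear contrasts of means, whereas the stated Wilcoxon test and the proposed replacement are rank-based. Simulated power (5,000 replicates, 25 per arm, 0.8 SD effect; for the skewed case, ρ and the effect are on the log scale of log-normal data):

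| Data, ρ | Wilcoxon, post | Interaction | Linear ANCOVA | Rank ANCOVA |
|---|---|---|---|---|
| Normal, 0 | 0.77 | 0.50 | 0.79 | 0.77 |
| Normal, 0.3 | 0.77 | 0.64 | 0.82 | 0.80 |
| Normal, 0.5 | 0.77 | 0.80 | 0.89 | 0.86 |
| Normal, 0.7 | 0.77 | 0.95 | 0.97 | 0.95 |
| Skewed, 0.3 | 0.76 | 0.54 | 0.62 | 0.80 |
| Skewed, 0.5 | 0.76 | 0.63 | 0.68 | 0.86 |
| Skewed, 0.7 | 0.76 | 0.79 | 0.79 | 0.95 |

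With no true effect and ρ = 0.5, all four methods rejected in 3.6% to 5.0% of replicates. Linear ANCOVA loses to Wilcoxon on skewed data at ρ = 0.3 and 0.5; rank ANCOVA does not. On normal data at ρ = 0.7, rank ANCOVA and the interaction are practically equal.

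**Effect of a baseline shifted by knowledge of allocation.** Suppose that reported baseline differs between arms by 0.2 SD for this reason alone. The bias is about ρ × 0.2 = 0.10 SD for the adjusted comparison at ρ = 0.5, the full 0.2 SD for the interaction, and none for the post-only Wilcoxon test.

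**The case against.** The strongest reply is that the article makes no error here. It matches recognised tests to types of data in one sentence, does not assign the TOP to any of them, and may leave model details to an analysis plan that is not shown. Even the primary test is unadjusted; adjustment enters only through the reported odds ratio. All of this is correct. It limits the point to an improvement in precision for one secondary outcome.

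A reader might go further and infer any of the following, none of which the article supports.

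- *That every reading of the sentence wastes the baseline.* Binary TOP items could go to Fisher's test. A mixed model with the arms' baseline means constrained equal is as efficient as ANCOVA, and the sentence does not exclude it.
- *That adjustment costs nothing.* It loses about 2% at zero correlation. Also, baseline is self-reported after open-label randomization, so knowledge of allocation could shift it. Only the post-only Wilcoxon test is immune to that; the interaction suffers more than the adjusted analysis.
- *That the gain is a known quantity*, such as one third more participants (1/0.75 = 1.33). That figure holds only for a linear contrast at an assumed correlation of 0.5.
- *That the stated tests are invalid.* They are not.

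What remains is that the article does state methods for these outcomes, that in their usual form they are the less precise ones, and that it endorses the benefit of baseline adjustment for its primary outcome.

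**Conclusion.** The point holds as a low-severity improvement. For non-binary TOP scores with a correlation strictly between 0 and 1, and a baseline unaffected by allocation, a baseline-adjusted comparison is more precise in large samples than either the post-only comparison or the unconstrained interaction. The size rests on the assumed correlation and on equal SDs; the percentages are for linear contrasts. In the simulations, rank ANCOVA keeps a gain over Wilcoxon at correlations of 0.3 to 0.7 for both normal and skewed data. Its gain over the interaction is clear except for normal data at 0.7, where it all but disappears.

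More precision does not repair the different assessment days. Any effect of measuring the experimental arm a day later than the control arm remains in the contrast, whichever method is used.

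**What to change.** Add a sentence to the secondary analysis section. For each non-binary TOP score to be analysed, compare post-induction values between arms by rank ANCOVA or a proportional-odds model with arm and baseline TOP as covariates. A mixed model with arm baseline means constrained equal is an acceptable alternative where the scores are not markedly skewed. Keep Wilcoxon–Mann–Whitney for the TPQ, which has no baseline, and Fisher's test for binary items.

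Either have participants complete the baseline TOP before their allocation is disclosed or, where that is not possible, report the unadjusted Wilcoxon test on post-induction values as a sensitivity analysis. State the day 3 versus day 2 difference as a limitation of the comparison.

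The cost is analysis wording and, if chosen, a change in the order of baseline procedures. No new data or visits are needed, because baseline TOP is already collected.
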